#### Secondary endpoints

The main secondary endpoint is 16S rRNA assessed in microbial testing of sputum, which is a measurement of airway bacterial colonization in NCFB. The levels of inflammatory factors, including interleukin-1-beta (IL-1β) [26], interleukin-8 (IL-8) [27], tumour necrosis factor-alpha (TNF-α) [28] and matrix metalloproteinase-9 (MMP-9) [29], and the levels of oxidative stressors, such as myeloperoxidase (MPO) [30], total antioxidant capacity (TAC) [31], superoxide dismutase (SOD) [32] and malondialdehyde (MDA) [20], in sputum and serum will also be detected through enzyme-linked immunosorbent assays (ELISAs) (Table 2).

#### Other variables

Baseline information will be collected at the time of enrolment (Table 3). Bronchiectasis severity index (BSI) scores, modified British Medical Research Council (mMRC) dyspnoea scores, HRCT grades and lung function parameters will facilitate further subgroup comparisons among patients with various pulmonary impairments. BSI scales will assess the NCFB severity by 9 items and divide it into 3 grades: low BSI score (0–4 points), moderate BSI score (5–8 points) and high BSI score (≥9 points) [33]. mMRC dyspnoea scales will be applied to patients with breathlessness [34]. The incidence of hospitalization, systemic glucocorticoid, and oral/intravenous antibiotic utilization 12-months before the enrolment and during the trial will also be monitored and recorded on CRFs (Table 2).

**Table 3 Tab3:** Information at baseline and evaluation of adverse events

Variable	Baseline (0-week)	1-month follow-up (4-weeks)	3-month follow-up (12-weeks)	6-month follow-up (26-weeks)	9-month follow-up (38-weeks)	12-month follow-up (52-weeks)
Baseline						
Age	X					
Gender	X					
City of residence	X					
Educational level	X					
Work activity	X					
Body Mass Index (BMI)	X	X	X	X	X	X
Smoking status	X	X	X	X	X	X
Alcohol status	X	X	X	X	X	X
Hazardous substance exposure	X	X	X	X	X	X
Hereditary diseases	X					
Comorbidity	X	X	X	X	X	X
Concomitant medication	X	X	X	X	X	X
Adverse events						
Allergy	X	X	X	X	X	X
Electrocardiogram (ECG)	X			X		X
Gastrointestinal toxicity^a^	X	X	X	X	X	X
Renal toxicity^a^	X	X	X	X	X	X
Hematological toxicity^a^	X			X		X
Biochemical toxicity^a^	X			X		X

X means items should be evaluated or detected at the current follow-up

^a^Variables consist of clinical manifestation assessing (including nausea, vomit, abdominal distension, abdominal pain and so on) and blood tests results (containing red blood cells counts, aspartate aminotransferase/Alanine aminotransferase (AST/ALT), creatinine and others)

### Adverse events

The safety of NAC will be evaluated during the whole follow-up period. Participants will receive study information containing explicit details on whom to contact in case of adverse events (AEs). Three respiratory specialists will judge the relationship between AEs and intervention drugs and will record the dates, solutions, endings and conclusions on the CRFs. Patients with AEs will be told to discontinue the study once the causality is determined (Table 3).

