**Methods:**

NINCFB is a prospective, multicentre, double-blind, randomised, placebo-controlled trial that will recruit 119 patients with NCFB and randomly divide them into an NAC group (*n* = 79) and a control group (*n* = 40). Participants in the NAC group will receive 600 mg oral NAC twice daily for 52 weeks, while patients in the control group will receive 600 mg placebo twice daily for 52 weeks. The information at baseline will be collected once participants are enrolled. The primary endpoints are the changes in St George’s Respiratory Questionnaire scores and the number of exacerbations in 52 weeks. The secondary endpoints are the 16S rRNA of sputum and the levels of inflammatory factors and oxidative stressors in sputum and serum. Other data related to radiography, lung function tests, number of oral and/or intravenous antibiotic therapies and adverse events (AEs) will also be analysed. Further subgroup analysis distinguished by the severity of disease, severity of lung function, airway bacterial colonization and exacerbation frequency will be performed.

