### Study design and intervention

NINCFB is a prospective, multicentre, double-blind, randomised, parallel, placebo-controlled trial studying NCFB in Chengdu city, Sichuan Province of China (Fig. 1). It is recruiting 119 patients with NCFB from 6 hospitals located in Chendu city and randomly (2:1) assigning these patients into an N-acetylcysteine (NAC) group (*n* = 79) and a control group (*n* = 40). Participants in the NAC group will be given oral N-acetylcysteine (produced by Hainan Zambon Pharmaceutical Co., Ltd.; national medicine permission number: H20000471; 600 mg, twice daily) for 52 weeks, while the control group will receive oral placebo (produced by Hainan Zambon Pharmaceutical Co., Ltd.; 00520C0; 600 mg, twice daily) for 52 weeks. All the participants will be followed up throughout the intervention period and will be required to provide relevant information about their demography, aetiology, symptomatology, bacteriology and radiography. The results will be analysed and presented in other papers. Study enrolment started on 3 March 2021 and is expected to be completed on 31 December 2024.

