### Data collection

Two clinical researchers at West China Hospital of Sichuan University will collect the data and make appointments for the following dates at the end of the first meeting to promote participant retention. A monitoring team consisting of 2 respiratory physicians and 1 investigator will verify and revise the results, it is independent from the sponsor and competing interests. Peripheral blood tests, electrocardiogram (ECG) readings, spirometry and HRCT scans for all the subjects will be conducted by laboratory experts and radiologists at West China Hospital of Sichuan University. All data collected both on paper and in electronic archives will be marked with a study identification number to confirm participants and will be stored in a locked cabinet and hospital computer system. Once recorded, the data will be locked to prevent changes. Missing data because of “no-shows” will be coded as incomplete. Access to the identified information sets will be limited to the study authors.

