### Sample size

We calculate the sample size required for the evaluation of primary outcome-1 (SGRQ scores) and primary outcome-2 (number of exacerbations) respectively. As NAC is effective in reducing sputum of patients with NCFB in clinical practice, we design a ratio of 2:1 for the sample size of intervention group to control group in this study so that two-thirds of enrolled patients could receive effective treatments. For the SGRQ score, we regard mean difference (MD) of 6 points of SGRQ score as the smallest clinically important difference between two group with a standard deviation (SD) of 8.5 used in the calculation, according to the previous report of NAC on patients with COPD [35–37]. Based on 90% power with a two-sided significance level of 5%, a sample size of 64 for intervention group and 32 for control group is needed as calculated by the software PASS 15. In addition, assuming 20% of patients in each group may drop out or lose data integrity, we need to recruit 79 in the intervention group and 40 in the control group. For the number of exacerbation, we regard MD of 0.7 times of exacerbation per year as the smallest clinically important difference between two group with a SD of 1 used in calculation, according to the published study of NAC on patients with postinfection or idiopathic bronchiectasis [21]. Considering 20% dropout, we also need to recruit 79 patients in NAC group and 40 patients in placebo group (α = 0.05, 1 - β = 0.9). Taken together, this study eventually aims to enroll 119 participants, of them, 79 in the NAC group and 40 in the placebo group.

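### Patients with a drug-related adverse event are told to leave the study rather than stop the drug, which conflicts with follow-up of all participants and can lose outcomes unequally between arms

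*Protocol article*

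**What the plan says.** In the protocol article, Adverse events describes two steps. First, "Three respiratory specialists will judge the relationship between AEs and intervention drugs", and the dates, management, outcome and conclusion go on the case report form. Then comes the rule at issue: "Patients with AEs will be told to discontinue the study once the causality is determined". No severity threshold is attached.

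Other places describe complete follow-up:

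- Study design and intervention: "All the participants will be followed up throughout the intervention period".
- The opening of Adverse events: "The safety of NAC will be evaluated during the whole follow-up period".
- Tables 2 and 3 schedule SGRQ, exacerbation and adverse event assessments up to week 52, with no exception for patients who had a related event.
- Abstract, Methods: "The primary endpoints are the changes in St George’s Respiratory Questionnaire scores and the number of exacerbations in 52 weeks".

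On missing data, Data collection says only "Missing data because of “no-shows” will be coded as incomplete". Sample size allows for loss by "assuming 20% of patients in each group may drop out or lose data integrity", the same fraction in both arms.

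**The concern.** Stopping a drug and leaving a trial are different events. A patient who stops drug can still complete questionnaires, report exacerbations and be watched for later harm. A patient told to leave the study cannot. The rule therefore removes outcome data after the exit, and the reason for exit is an event attributed to treatment. If NAC causes more such events than placebo, the loss is unequal by design. Three things are at stake:

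- **Exacerbations.** Statistical analysis compares the primary outcomes by t test or Wilcoxon test. A patient who leaves early has less time in which to be counted. More early exits on NAC lower the NAC count with no true effect, so the error favours NAC.
- **SGRQ at week 52.** The comparison would cover only those who stayed. The direction of bias depends on how the leavers would have scored.
- **Safety.** The triggering event and its outcome are still recorded, but separate events after exit are not seen. Long-term adverse effects are a stated study objective.

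An analysis plan can adjust exacerbation counts for time at risk. It cannot recover SGRQ scores or safety data that were never collected.

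**Working it through.** **The text.** The sentence before the rule refers to the intervention drugs, so the article had a term for the medication. The rule itself names the study. Nothing in the article says that these patients remain in follow-up. A patient who obeys the rule cannot also be followed through the intervention period, so the two statements cannot both hold for that patient.

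**The plan's sample size.** With 2:1 allocation, two-sided 5% and 90% power, the control arm needs 1.5 × (1.960 + 1.282)² × (SD/MD)².

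- SGRQ, MD 6 and SD 8.5: 1.5 × 10.51 × 2.007 = 31.6, so 32 control and 64 NAC, as stated.
- Exacerbations, MD 0.7 and SD 1: 1.5 × 10.51 × 2.041 = 32.2, so 33 and 66 by strict rounding.
- Dropout of 20%: 32/0.8 = 40 and 64/0.8 = 80, against 40 and 79 stated.

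The planned 119 is reproduced to within a patient or two. The point does not dispute it.

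**Assumptions for the size of the effect.** The documents give no rate of related adverse events, so these are choices, not data:

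- Exit under the rule: 10% NAC and 3% placebo, or 15% and 5%. That is 79 × 0.10 ≈ 8 to 79 × 0.15 ≈ 12 NAC patients, and 40 × 0.03 ≈ 1 to 40 × 0.05 = 2 placebo patients. All fit inside the 20% allowance.
- Exit time uniform over 52 weeks, so a leaver loses half the year on average.
- Exacerbations: mean 2 per year in both arms (no true effect), negative binomial with dispersion 0.3.

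**Exacerbation count.** Expected shift = −2 × (pNAC − pPlacebo) × 0.5.

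- 10%/3%: −2 × 0.07 × 0.5 = −0.07, and 0.07/0.7 = 10% of the target.
- 15%/5%: −2 × 0.10 × 0.5 = −0.10, and 0.10/0.7 = 14% of the target.

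Simulation of 40,000 trials, 79 against 40, raw counts compared by pooled t test:

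| Exit NAC / placebo | Mean shift | Two-sided type I error | False result favouring NAC |
|---|---|---|---|
| 0% / 0% | 0.00 | 5.2% | 2.7% |
| 5% / 2% | −0.03 | 5.2% | 3.3% |
| 10% / 3% | −0.07 | 5.5% | 4.2% |
| 15% / 5% | −0.10 | 5.9% | 4.8% |
| 10% / 10% | 0.00 | 5.0% | not given |
| 15% / 15% | 0.00 | 4.8% | not given |

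Repeat runs agreed to within about 0.3 percentage points. For example, one gave 6.0% and 5.1% at 15%/5%. The shift is proportional to the exacerbation rate. At 1 per year it halves, to about −0.03 to −0.05.

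The simulated variance is 2 + 0.3 × 2² = 3.2, an SD of 1.79, which is wider than the SD of 1 in Sample size. The standard error of the difference is SD × √(1/79 + 1/40) = SD × 0.194. A shift of 0.07 is then 0.07/0.347 = 0.20 standard errors here, and 0.07/0.194 = 0.36 at the plan's SD. On that score the table is not a worst case.

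**SGRQ among completers.** If leavers in either arm would have scored D points worse than those who stayed, the bias in favour of NAC is (pNAC − pPlacebo) × D.

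- 0.07 × 4 = 0.28 points, and 0.28/6 = 5% of the target.
- 0.10 × 8 = 0.80 points, and 0.80/6 = 13% of the target.
- It is zero if D = 0, and reversed if leavers would have scored better.

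**Power.** With all 79 and 40 observed, noncentral-t power is 95.0% for SGRQ and 94.7% for exacerbations. If the rule adds 10 points of loss on NAC beyond the planned 20% (55 against 32 evaluable), power is 88.1% and 87.5%. Precision is not the main problem.

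**The case against.** The strongest objection is that the sentence is loose English for stopping the drug. The article is a condensed account, its wording is imprecise elsewhere, and detailed withdrawal rules normally sit in the full protocol. The general follow-up statement and the week-52 visits can be read as support for that intention. This may be what the authors meant, and it limits confidence. But the point concerns a rule that is stated, not one left out. No part of the article supplies the milder reading, and staff who follow the text would withdraw the patient.

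The second objection is that harm is assumed. This stands in part. No adverse event rates are given, relatedness is judged while researchers are blinded so placebo patients may also be withdrawn, and equal exit produces no shift. At 5%/2% exit the two-sided error does not move. The figures show what could happen, not what will.

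The third is that the exacerbation bias depends on the analysis. This also stands in part. Exit dates would allow a rate, and Table 2 collects time to first and second exacerbation. An unseen analysis plan may use them. That does not help the week-52 SGRQ score or later safety.

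**Conclusion.** The concern holds. As written, the rule ends follow-up for patients whose adverse event is judged related to study drug, and it contradicts the article's own statements on follow-up. Under the assumed excess exit on NAC of 7 to 10 percentage points, the raw exacerbation difference moves by 0.07 to 0.10 towards NAC, and the chance of a false result favouring NAC rises from about 2.7% to between 4% and 5%. The SGRQ difference could move by 0.3 to 0.8 points. These sizes rest on assumed exit rates, exit times, exacerbation rate and leaver scores, and on counts not adjusted for exposure. The bias is modest against the targets of 0.7 and 6. It should be fixed because the loss is avoidable and the clinical rule does not require it. Confidence is medium, since the authors may have meant only that drug is stopped.

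**What to change.** Replace the sentence in Adverse events with, for example:

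> *Patients with an adverse event judged related to study drug will discontinue study drug. Unless consent is withdrawn, they continue all scheduled SGRQ, exacerbation and adverse event assessments to week 52.*

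Analyse the data collected after stopping drug in the assigned arm. When to stop drug remains a clinical decision. If the full protocol already keeps these patients in follow-up, correcting the article to match is enough.

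The cost is one change of wording. Tables 2 and 3 already schedule the visits, and the sample size does not change.

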### Data collection

Two clinical researchers at West China Hospital of Sichuan University will collect the data and make appointments for the following dates at the end of the first meeting to promote participant retention. A monitoring team consisting of 2 respiratory physicians and 1 investigator will verify and revise the results, it is independent from the sponsor and competing interests. Peripheral blood tests, electrocardiogram (ECG) readings, spirometry and HRCT scans for all the subjects will be conducted by laboratory experts and radiologists at West China Hospital of Sichuan University. All data collected both on paper and in electronic archives will be marked with a study identification number to confirm participants and will be stored in a locked cabinet and hospital computer system. Once recorded, the data will be locked to prevent changes. Missing data because of “no-shows” will be coded as incomplete. Access to the identified information sets will be limited to the study authors.

### Statistical analysis

The resulting data will then be analysed with SPSS V.26 by statistical experts. Primary outcomes of each group will be compared by Student’s t test (t test) or the Wilcoxon rank-sum test after calculating its normal distribution and will be expressed in terms of the mean, standard deviation (SD) or median to indicate the long-term efficacy of NAC for NCFB. The comparison between the NAC group and the control group in terms of 16S rRNA and the levels of inflammatory factors and oxidative stressors will be of vital importance. In addition, NINCFB will also use the t-test, chi-square test and Wilcoxon rank-sum test to evaluate baseline discrepancy and other variables. Regression analysis and the correlation coefficient may confirm the predictors of disease progression and indicators of NAC efficacy.

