### Outcome measures

All outcome measures will be recorded at baseline and during the intervention period (Table 2).

**Table 2 Tab2:** Study main measures and outcomes to be collected

Variable	Baseline (0-week)	1-month follow-up (4-weeks)	3-month follow-up (12-weeks)	6-month follow-up (26-weeks)	9-month follow-up (38-weeks)	12-month follow-up (52-weeks)
Primary Endpoint 1						
SGRQ scores	X	X	X	X	X	X
Primary Endpoint 2						
Number of exacerbations during the follow-up		X	X	X	X	X
Secondary Endpoints						
16S rRNA sequencing of sputum	X			X		X
Inflammatory factors	X			X		X
Oxidative stressors	X			X		X
Other Variables						
Clinical signs and symptoms	X	X	X	X	X	X
Transcutaneous regional oxygen saturation	X	X	X	X	X	X
BSI scores	X	X	X	X	X	X
mMRC dyspnea scores	X	X	X	X	X	X
HRCT grade, n (%)	X					X
Number of lesion lobes, n (%)	X					X
FEV1/FVC%	X			X		X
FEV1%	X			X		X
Number of exacerbations 12-months before the enrollment and during the trail	X	X	X	X	X	X
Time to first exacerbation		X	X	X	X	X
Time to second exacerbation		X	X	X	X	X
The longest duration of exacerbation in the last year	X					
The longest duration of exacerbation during the follow-up		X	X	X	X	X
Number of oral antibiotic therapies 12-months before the enrolment and during the trail	X	X	X	X	X	X
Number of intravenous antibiotic therapies 12-months before the enrolment and during the trail	X	X	X	X	X	X
Number of systemic glucocorticoid utilization12-months before the enrolment and during the trail	X	X	X	X	X	X
Number of hospitalization 12-months before the enrolment and during the trail	X	X	X	X	X	X

X means items should be evaluated or detected at the current follow-up

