#### Primary endpoints

The primary endpoints of the NINCFB are quality of life (St George’s Respiratory Questionnaire, SGRQ scores) and the number of exacerbations during the follow-up period. The SGRQ, a comprehensive questionnaire to estimate pulmonary symptoms and living conditions, is commonly used to assess a patient’s quality of life [22, 23] and has good psychometric properties for the NCFB [24]. Exacerbation of NCFB is defined by the British Thoracic Society as acute deterioration (usually over several days) with worsening local symptoms (cough, increased sputum volume or change in viscosity, increased sputum purulence with or without increasing wheezing, breathlessness, or haemoptysis) and/or systemic upset [25]. This study has two variables designed to determine whether the long-term effectiveness of NAC achieves the treatment goal of NCFB (Table 2).

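### The SGRQ primary comparison names no baseline covariate and leaves open score or change, the visit, and the basis of the SD of 8.5; a baseline-adjusted analysis is a free improvement

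*Protocol article*

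**What the plan says.** All places are in the protocol article.

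- **Test.** Statistical analysis: "Primary outcomes of each group will be compared by" a t test or a Wilcoxon rank-sum test, the choice following a check of normality. No covariate, visit or repeated-measures term is attached.
- **Endpoint as change.** Abstract, Methods: "The primary endpoints are the changes in St George’s Respiratory Questionnaire scores and the number of exacerbations in 52 weeks".
- **Endpoint as score.** The Primary endpoints section opens with "The primary endpoints of the NINCFB are quality of life" and gives SGRQ scores in parentheses. The Sample size section refers to "primary outcome-1 (SGRQ scores) and primary outcome-2 (number of exacerbations) respectively".
- **Schedule.** Outcome measures: "All outcome measures will be recorded at baseline and during the intervention period". Table 2 lists SGRQ at baseline and at weeks 4, 12, 26, 38 and 52.
- **Planning values.** Sample size: difference 6 points, SD 8.5, two-sided 5%, 90% power, 2:1 allocation, 64 and 32 evaluable, 79 and 40 recruited after allowing 20% for dropout or lost data. The SD is not identified as that of a score or of a change.
- **Missing visits.** Data collection: values lost to no-shows "will be coded as incomplete".

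**The concern.** Three things that together define the SGRQ analysis are left open: whether a score or a change is compared, at which visit, and which of the two the SD of 8.5 describes. The choice of test is not left open. The article names a plain two-group comparison, so this is a stated choice and not a detail deferred to another document.

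Two consequences follow. First, if baseline and follow-up SDs are equal, scores and changes share one SD only when their correlation is 0.5. At any other value, a sample size computed for one variable has a different power when the other is tested. Second, even with matching inputs, the named test is less precise than one that adjusts for the baseline SGRQ value, which every patient is scheduled to provide. What is at stake is the precision and the reproducible definition of a primary endpoint. In a randomised comparison the unadjusted test is unbiased, so validity is not in question.

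**Working it through.** **Inputs from the Sample size section:** difference 6, SD 8.5, two-sided alpha 0.05, power 90%, evaluable 64 and 32.

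**Assumed, not in the article:** the correlation r between baseline and follow-up SGRQ, taken from 0.3 to 0.8, and equal SDs at both times.

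**Step 1: reproduce the plan.**

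Control n = (1 + 1/2) × (1.960 + 1.282)² × (8.5/6)² = 31.6, so 32, with 64 on NAC. This is the stated size.

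Standard error = 8.5 × √(1/64 + 1/32) = 8.5 × 0.2165 = 1.840, and 6/1.840 = 3.26. Power is 90.3% by the normal approximation and 89.7% by the noncentral t. The stated 90% is met when 8.5 is the SD of the variable tested.

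**Step 2: variances.** With score SD s:

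- score: s²
- change: 2s²(1 − r)
- ANCOVA residual: s²(1 − r²)

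ANCOVA relative to change is (1 − r²)/[2(1 − r)] = (1 + r)/2. That is 0.75 at r = 0.5 and 0.90 at r = 0.8, a reduction of 25% to 10%. ANCOVA relative to score is 1 − r². That is 0.75 at r = 0.5 and 0.36 at r = 0.8, a reduction of 25% to 64%. For any r strictly between 0 and 1, ANCOVA has the smallest variance of the three.

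**Step 3: power at 64 and 32 for 6 points (noncentral t).**

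Reading A, 8.5 is the SD of change. Score SD = 8.5/√[2(1 − r)]. A t test on change has 89.7% at every r.

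| r | score SD | t test on score | ANCOVA SD | ANCOVA |
|---|---|---|---|---|
| 0.3 | 7.18 | 96.8% | 6.85 | 97.9% |
| 0.4 | 7.76 | 94.2% | 7.11 | 97.1% |
| 0.5 | 8.50 | 89.7% | 7.36 | 96.1% |
| 0.6 | 9.50 | 82.3% | 7.60 | 95.0% |
| 0.7 | 10.97 | 70.5% | 7.84 | 93.8% |
| 0.8 | 13.44 | 53.2% | 8.06 | 92.5% |

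Reading B, 8.5 is the SD of the score. Change SD = 8.5 × √[2(1 − r)]. A t test on the score has 89.7% at every r.

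| r | change SD | t test on change | ANCOVA SD | ANCOVA |
|---|---|---|---|---|
| 0.3 | 10.06 | 77.9% | 8.11 | 92.3% |
| 0.4 | 9.31 | 83.8% | 7.79 | 94.1% |
| 0.5 | 8.50 | 89.7% | 7.36 | 96.1% |
| 0.6 | 7.60 | 95.0% | 6.80 | 98.1% |
| 0.7 | 6.58 | 98.6% | 6.07 | 99.5% |
| 0.8 | 5.38 | 99.9% | 5.10 | >99.9% |

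The ANCOVA columns ignore the one degree of freedom spent on the covariate, which moves none of them by more than about 0.01 percentage points. The Wilcoxon branch was not modelled.

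**The case against.** The strongest reply is that the plan is coherent as it stands. The sample size reproduces for exactly the t test that the article names, and type I error already allows for chance baseline imbalance. The Bias control section also promises multivariate analysis, and a condensed article may leave covariates and repeated-measures models to the full protocol or SAP. Much of this stands. The remaining criticism of the method concerns efficiency, and over a change-score test the gain is moderate. The Bias control sentence, however, names no covariate and is not tied to SGRQ or to the primary test, so it does not alter the comparison that the article specifies.

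Four stronger readings are tempting, and the document does not support them.

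- **Baseline is ignored.** This is true only if raw scores are tested. The abstract says change, and a test on change does use baseline, though less efficiently than ANCOVA.
- **Four of the five follow-up visits are thrown away.** No section says that a single visit is analysed. What can be said is that the visit is not fixed.
- **The trial is underpowered.** A shortfall needs both a mismatch between SD and endpoint and a correlation on the unfavourable side of 0.5. On the other side, a mismatch raises power.
- **Patients who miss week 52 will be excluded.** The article describes how no-shows are coded, not who is analysed. A week-52 t test would lose them, but the article does not say that this is the analysis.

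**Conclusion.** The point holds as a free improvement that should be made; it is not an error that undermines the trial. The article names a two-group SGRQ comparison without a baseline covariate, gives the endpoint as change in one place and score in two others, and states neither the visit nor the basis of the SD. With matching inputs the planned power of about 90% is reached.

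Under mismatch, power falls to 82%, 71% and 53% at correlations 0.6, 0.7 and 0.8 (scores tested, 8.5 for change), or to 84% and 78% at 0.4 and 0.3 (change tested, 8.5 for score). Baseline adjustment keeps power at 92% or more under both readings across 0.3 to 0.8, so its benefit does not depend on settling what 8.5 meant. These figures rest on the assumed correlations, equal SDs at the two times, the stated 64 and 32 evaluable patients, and a true difference of 6 points.

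**What to change.** 1. Define one SGRQ primary endpoint in the same words in the abstract, Primary endpoints, Statistical analysis and Sample size sections: change from baseline in SGRQ total score at week 52.
2. State in the Sample size section whether 8.5 is the SD of that change or of a score.
3. For SGRQ, replace the t-test/Wilcoxon choice with a baseline-adjusted analysis. ANCOVA at week 52 with baseline SGRQ as covariate is enough. A mixed model for repeated measures is the alternative, with treatment, visit, treatment-by-visit and baseline SGRQ, and the week-52 contrast as primary. It also uses the earlier visits of patients who miss week 52.

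The cost is wording only. Table 2 already schedules every value needed, and no extra patients or visits are required. The Randomisation and double-blind section starts unblinding and analysis only after all follow-up is finished, so the change should be made and dated before then.

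### The t-test branch is Student's pooled-variance test in a 2:1 trial; naming the Welch version would protect it against unequal arm variances at almost no cost

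*Protocol article*

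**What the plan says.** The Statistical analysis section states that primary outcomes will be "compared by Student’s t test (t test") or by the Wilcoxon rank-sum test, the choice following a check of normality. The t test is named again, with the chi-square and Wilcoxon tests, for baseline comparisons and the other variables. The data will be "analysed with SPSS V.26 by statistical experts". The section mentions no unequal-variance version, no check of variances and no confidence interval.

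The Study design and intervention section describes "randomly (2:1) assigning these patients into an N-acetylcysteine (NAC) group", and the Sample size section repeats it: "we design a ratio of 2:1 for the sample size of intervention group to control group". That section plans with one SD per endpoint: for SGRQ a "standard deviation (SD) of 8.5 used in the calculation", and for exacerbations an SD of 1. It gives no SD by arm.

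**The concern.** Student's t test estimates one common variance and applies it to both arms. With equal arm sizes it makes little difference if the true variances differ, because the pooled standard error still equals the correct one. With 2:1 allocation the pooled variance is dominated by the larger NAC arm, while the smaller placebo arm contributes more to the uncertainty of the difference. If the placebo arm is the more variable, the standard error is too small and the test rejects too often. If the NAC arm is the more variable, for instance because only some patients respond, the standard error is too large and power is lost.

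Unequal spread is possible here. The Study objective and Subgroup analysis sections anticipate that the effect of NAC may differ by severity, cause and colonisation, and such heterogeneity would usually change the variance in the NAC arm. At stake are the calibration of the p value for any outcome that goes through the t-test branch, SGRQ being the natural candidate, and of any interval built on the same standard error.

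**Working it through.** **Inputs from the Sample size section.** SGRQ difference 6, SD 8.5; exacerbation difference 0.7, SD 1; two-sided 5%; 90% power; 2:1; 64 NAC and 32 control evaluable; 79 and 40 recruited.

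**Assumption, not in the article.** Ratio r of control SD to NAC SD, varied from 0.5 to 2.

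**1. The plan's own figure.** With the normal approximation, control n = (1 + 1/2) × (1.960 + 1.282)² × SD² / difference².
- SGRQ: 1.5 × 10.51 × 72.25 / 36 = 31.6, so 32 control and 64 NAC. This matches the article. Power from the equal-variance noncentral t at 64:32 is 89.7%.
- Exacerbations: 1.5 × 10.51 × 1 / 0.49 = 32.2, so 33 and 66. At 64:32 the noncentral t power is about 89.3%.
- Dropout of 20%: 64/0.8 = 80 and 32/0.8 = 40, against the stated 79 and 40.

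The stated size is therefore reproduced closely, under a common SD in both arms.

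**2. Standard errors when the SDs differ** (NAC SD set to 1, control SD = r).
- Pooled SE = sqrt{ [(63 + 31r²)/94] × (1/64 + 1/32) }
- Correct SE = sqrt(1/64 + r²/32)

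At r = 1.5:
- Pooled SE = sqrt[(63 + 31 × 2.25)/94 × (1/64 + 1/32)] = 0.257.
- Correct SE = sqrt(1/64 + 2.25/32) = 0.293.
- Ratio = 0.88, so Student's test uses 88% of the correct SE.

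At 48:48 both expressions reduce to sqrt[(1 + r²)/48]. The ratio is exactly 1 whatever r is, so the sensitivity comes from the 2:1 split.

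**3. Type I error for equal means.** Simulated normal data, at least 400,000 replicates per setting, two-sided 5%:

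| r (control SD / NAC SD) | Student, 64:32 | Welch, 64:32 | Student, 79:40 |
|---|---|---|---|
| 0.5 | 1.7% | 5.0% | 1.7% |
| 0.67 | 2.6% | 5.0% | 2.7% |
| 0.8 | 3.5% | 5.0% | 3.5% |
| 1 | 5.0% | 5.0% | 5.0% |
| 1.25 | 6.9% | 5.0% | 6.9% |
| 1.5 | 8.5% | 5.0% | 8.4% |
| 2 | 11.1% | 5.0% | 10.9% |

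The large-sample formula 2 × [1 − Φ(1.96 × pooled SE / correct SE)] agrees. At r = 1.5 it gives 2 × [1 − Φ(1.96 × 0.878)] = 8.5%. At 48:48, Student's test stays at about 5.1% for r from 0.5 to 2.

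**4. What Welch costs if the SDs are equal, at 64:32.**
- SGRQ: 89.4% power against 89.7%.
- Exacerbations: about 89.0% against 89.3%.

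The loss is about 0.3 points; a separate simulation put it at about 0.4 for SGRQ (89.4% against 89.8%).

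**The case against.** **Student's test is not the only test.** It is one of two branches, and Wilcoxon is used if the data do not look normal. Exacerbation, antibiotic and hospitalisation counts are discrete and usually skewed, so they would probably go to Wilcoxon, where Welch is no remedy. This stands and limits the point to the t-test branch.

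**Nothing shows unequal variances.** A reader might infer that the p values and error bars will be wrong. The article does not support that: it gives one SD per endpoint, and the ratios in the table are assumptions. With equal SDs Student's test is exact. This stands.

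**A false-positive claim needs care.** If NAC affects no patient, randomisation gives both arms the same distribution, hence the same variance, and the type I error stays at 5%. The inflated figures need a treatment that changes the spread but leaves the means equal. One might also argue that counts err in a known direction, since variance tends to rise with the mean and placebo is expected to have the higher mean. That operates only when NAC has an effect and a t test is applied, so it bears on interval coverage and not on false positives. It also needs arm means that the article does not give, since only the difference of 0.7 is stated.

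**Intervals.** No confidence interval is mentioned, so coverage matters only if one is reported from the pooled standard error. This stands.

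**Condensed article.** The named test may be a generic label, and the version used could be settled in a fuller document. That is possible, and it lowers the severity. It does not remove the point: the article names a specific test, and a better one for unequal arms is available at negligible cost.

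**Conclusion.** The point holds as a low-severity improvement in robustness. For outcomes that reach the t-test branch, the named test is sensitive to unequal SDs because of the 2:1 split. Modest differences in spread (r from 0.8 to 1.25) move the type I error for equal means to between 3.5% and 6.9%; large ones (0.5 to 2) move it to between 1.7% and 11.1%. Welch holds 5% throughout.

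These figures rest on normal data and assumed SD ratios. They describe what happens if NAC changes the spread as well as, or instead of, the mean. They do not show that the planned analysis is in error, and they leave the stated sample size essentially unchanged.

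**What to change.** In the Statistical analysis section, replace Student's t test by the Welch (unequal-variance) t test wherever the t-test branch is used, for the primary outcomes and the other variables. State that the choice will not depend on a preliminary test of variances, and base any reported confidence interval for a mean difference on the same standard error. Settling this before unblinding also prevents a later choice between pooled and unpooled results.

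The cost is one phrase and about 0.3 to 0.4 percentage points of power at 64:32 if the SDs are equal (about 0.2 at 79:40). No extra patients or data are needed. Outcomes sent to the Wilcoxon test are not affected.
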